^a^Exclusion criteria is valid for the primary data analysis only. Low values indicate less pain and improved function: 0 points = no pain and maximum physical functioning respectivelyThe exercise intervention is accessible at 55 locations (study sites) of the country, offering 85 exercise courses each half year. The number of participants per exercise course is restricted to twelve persons. The recruitment period covers two course terms. Assuming twelve participants in each course, the intervention can be provided to approximately 2000 insurants. Eligible patients can participate on condition that their physicians prescribe the health care offer. Interested patients register for the intervention program at the location nearby and will be informed about the accompanying scientific evaluation of the exercise program. In this context, exclusion criteria are requested and only eligible patients will finally be allowed for the exercise intervention. Further details including the study information sheet for potential study participants, the informed consent and a check-list for all inclusion and exclusion criteria will be delivered by mail. This mail will be sent to each participant prior to the first training session. The mail further includes the self-administered questionnaires. In the context of all aforementioned stages it will be pointed out that study participation is not a presupposition for exercise participation. Eligibility of the patients to enter the exercise program and to participate in the study will finally be determined by checking the inclusion- and exclusion criteria for the exercise intervention 1st in the context of the first visit and 2nd by information recorded via the self-administered questionnaire at t0 (Table 1). Patients refraining from the study still are eligible to receive the exercise program.Feasibility of recruitmentWe estimate that the offered exercise courses will be booked by 1500 patients (corresponding to 75 % occupancy rate). We further estimate a pre-study drop-out rate of 50–60 % due to lack of interest in study participation or exclusion according to study criteria. Thus approximately 700 patients will be allocated to the trial.Recruiting and selection of the control group (CO)(1) In a first step the insurance ID of study participants will be forwarded to a specific department of the health insurance company. This department is responsible for the extraction of ten statistical controls for each study participant of the intervention group according to the procedure described in the statistical part of this manuscript. This pool of controls shall ensure the proper selection of one matched statistical twin for each participant in the second matching step according to number (5). The factor ten has already been proven successful in a previous study of the insurance company and was therefore adopted for the present study [18].(2) The address and insurance number of the selected statistical controls according to (1) will be forwarded to another department of the company. This department will then forward study details (study information sheet for participants, informed consent form, questionnaires) by mail in order to ask if they are willing to participate in the control group of the study.(3) Subsequently all duly completed questionnaires at t0 will be checked for in- and exclusion criteria which are part of the initial self-administered questionnaire (Table 1).(4) Included study participants will then be recontacted to ask for follow-up data at t3, t6 and t12 (follow-up data will be gathered from all controls as the availability of economic data at t0 is temporally delayed for 12 month for organizational reasons).(5) The final statistical twins (1:1 matching) will be selected using Propensity Score Matching (PSM). According to Austin, the propensity score can be explained as “the probability of treatment assignment conditional on observed baseline characteristics”. Matched-pairs are generated with nearest neighbor matching. “The nearest neighbor matching selects for matching to a given treated subject that untreated subject, whose propensity score is closest to that of the treated subject” [19]. Input variables for PSM are derived from the baseline data of the self-administered questionnaires (SAQ) as well as economic data from the insurance data base (IDB). The detailed matching procedure is described in the statistical part of this manuscript.Feasibility of recruitmentThe selection of statistical twins is designed according to a successful procedure of a previous study of the insurance company. In this study on the efficacy of an exercise program for patients with back pain, a responder rate of the controls of 60 % could be achieved [18].

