#### Matching procedures and statistical analysis of clinical endpoints

The matching procedure for the statistical twins of the control group (CO) will be conducted as followed: ten statistical controls for each participant of the intervention group will be selected from the insurance data base according to the matching criteria displayed in Table 5. If it is not possible to select ten matches for a subject of the intervention group according to the criteria and tolerances displayed in Table 5, the tolerance will be extended in an iterative manner (steps of 100 Euro or 1 day respectively) until ten controls can be extracted from the data base.

**Table 5 Tab5:** Matching criteria to extract 10 controls for each participant of the intervention

Criteria	Tolerance
Co-morbidity: Quantity of hierarchical ordered morbidity groups in the previous year	0
Osteoarthritis of the hip or knee joint in the previous year: yes/no	0
Participation in a special general practitioner care program (“Hausarztzentrierte Versorgung”): yes/no	0
Routine data: Age (years), gender, type of insurance (compulsorily insured, family insured, pensioner, unemployed), complexity of work (from 1 = low to 4 = high), level of education (1 = no graduation to 4 = High School), highest level of educational attainment (from 1 = no qualification to 6 = doctoral degree), contractual form (permanent/fixed term contract, full time/part time)	0
Joint replacement in the last 24 month prior t0 at the hip and/or knee joint(s): yes/no	0
Sum of unspecific health care costs (overall costs) in the last 24 month prior t0: Sick-pay, hospital costs, out-patient costs, costs related to periods of disability and costs related to drugs, physical modalities and adjuvants.	+/− 100 EUR
Sum of unspecific health care costs (overall costs) in the last 6 month prior t0 (tm6): Sick-pay, hospital costs, out-patient costs, costs related to periods of disability and costs related to drugs, physical modalities and adjuvants.	+/− 100 EUR
Sum of specific diagnosis (hip/knee OA) related health care costs in the last 24 month prior t0: Sick-pay, hospital costs, out-patient costs, costs related to periods of disability and costs related to disease related drugs, physical modalities and adjuvants such as walkers, cranks or orthotics.	+/− 100 EUR

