Sum of specific diagnosis (hip/knee OA) related health care costs in the last 6 month prior t0 (tm6): Sick-pay, hospital costs, out-patient costs, costs related to periods of disability and costs related to disease related drugs, physical modalities and adjuvants such as walkers, cranks or orthotics.	+/− 100 EUR
Disability days in the last 24 month prior t0 (tm24)	+/− 1 Day
Disability days in the last 6 month prior t0 (tm6)	+/− 1 Day
Specific disability days (hip/knee OA) days in the last 24 month prior t0 (tm24)	+/− 1 Day
Specific disability days (hip/knee OA) in the last 6 month prior t0 (tm6)	+/− 1 Day

Legend: a tolerance of “0” is equal to complete agreement, i.e. for age in years. Matching criteria are derived from the insurance data base

The matching process for the identification of statistical controls (CO) for each subject of the intervention group will be permuted in blocks: The matching procedure will be conducted quarterly until the number of needed subjects is reached.

Selected subjects will be asked for study participation (see section recruiting). The final statistical twins for each participant (1:1 matching) will be selected from all eligible responders. As a primary criterion, twins must be identical with regard to site(s) of OA (hip, knee or both). The following independent variables of the self-administered questionnaires (SAQ) and insurance data base (IDB) will then be used as input variables for the logistic regression of the PSM:Socio-demographic data at t0: age and gender (SAQ)Co-morbidity: Quantity of hierarchical ordered morbidity groups in the previous year (IDB)Osteoarthritis of the hip or knee in the previous year (IDB)WOMAC Index subscale pain at t0 (SAQ).WOMAC Index subscale physical functioning at t0 (SAQ).Quality Adjusted Life Years at t0 via VR-6D (SAQ).Body mass index at t0 (SAQ).Joint replacement hip and/or knee joint(s) at t0 (SAQ).General Self-Efficacy scale GSE at t0 (SAQ)Habitual physical and sports activity status at t0Participation in health activity programs (i.e. walking courses) at t0

If there are any cost/disability day categories, in which the standard mean differences after matching are above 0.05, a new matching will be conducted with these cost/disability day categories as matching variables in addition. No follow-up data will be analyzed prior to the final definition of the statistical twin of the CO for a given IG patient.

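### Six variables matched exactly in step one are left out of the final propensity score and of the balance check, so differential response among controls can unbalance them unnoticed

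*Protocol article*

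**What the plan says.** Matching has two steps.

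**Step one** (Statistics, Matching procedures, Table 5) draws ten controls per participant from the insurance data base. Eleven variables have tolerance 0. They include "Participation in a special general practitioner care program", contractual form, highest educational attainment and schooling, the last given as "level of education (1 = no graduation to 4 = High School". Insurance and work status are exact as well: "type of insurance (compulsorily insured, family insured, pensioner, unemployed), complexity of work (from 1 = low to 4 = high". Four cost sums and four disability-day counts are matched within tolerances that may be widened. Design, Recruiting and selection of the control group, step (1), gives the purpose: "This pool of controls shall ensure the proper selection of one matched statistical twin for each participant in the second matching step".

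**Step two** (same Statistics section) follows the mailing: "The final statistical twins for each participant (1:1 matching) will be selected from all eligible responders". One hard criterion applies: "As a primary criterion, twins must be identical with regard to site(s) of OA (hip, knee or both". The listed socio-demographic inputs to the propensity score are "Socio-demographic data at t0: age and gender (SAQ". The other inputs are morbidity count, osteoarthritis in the previous year, WOMAC pain and function, VR-6D, BMI, joint replacement, self-efficacy, activity status and participation in health programs. If a cost or disability-day category shows an SMD above 0.05 after matching, a new matching adds that category.

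The outcome model is linear with the propensity score as covariate. The sample size section declines a matched-pair analysis and relies on similar covariate distributions between groups.

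On economic inputs, step (5) of the recruitment section says that the score uses questionnaire data "as well as economic data from the insurance data base (IDB". The Statistics list contains no cost or disability-day variable unless the re-match rule is triggered.

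**The concern.** The study is not randomised, so covariate balance is its main protection against confounding. Step one secures exact balance on the six variables among the people who are mailed. The controls then pass a second filter, response and eligibility, which does not act on the intervention group: step one is run on intervention patients who are already study participants. If education, employment or insurance status influences who returns a postal questionnaire, the responding controls no longer mirror the intervention group on these variables. Twins may be drawn from all responders, so a twin need not come from its participant's own set of ten and can differ from that participant on any of the six.

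The plan has no later safeguard for them. They are not in the score, the stated balance limit does not reach them, and adjustment for a score that omits them does not correct for them. Education and type of employment plausibly relate to postal response, to self-reported symptoms and to disability days, so the question is not merely formal.

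**Working it through.** **1. Which Table 5 variables survive into step two**

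| Table 5 variable | In initial score? | Stated balance check? |
|---|---|---|
| Age, gender, morbidity count, OA in previous year, joint replacement (5, exact) | Yes (joint replacement as self-reported at t0) | Through the score |
| Four cost sums, four disability-day counts (8, with tolerance) | No | Yes, SMD above 0.05 triggers a re-match |
| Insurance type, complexity of work, education, attainment, contractual form, GP-centred care (6, exact) | No | None |

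So 5 + 8 + 6 = 19 variables, of which the initial score keeps 5. Of the 11 exact variables, 6 are neither carried forward nor checked. The iterative widening works in euros and days only, so it does not affect these six in step one.

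**2. How far response alone could move one of the six**

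Inputs: overall response R = 0.60 (recruitment section, from the insurer's earlier back-pain study). Prevalence p of a category from 0.2 to 0.5, and a response gap g between the category and the rest of 10 or 20 points, are assumptions; the protocol gives neither. No correction through correlated score variables is assumed.

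The category responds at r1 = R + g(1 − p), or R − g(1 − p) if it responds less. Its share among responders is q = p·r1/R. Then

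SMD = (q − p) / √{[p(1 − p) + q(1 − q)]/2}.

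Example, p = 0.4, g = 0.10, category responding more: r1 = 0.66, q = 0.4 × 0.66/0.60 = 0.44, SMD = 0.04/√[(0.24 + 0.2464)/2] = 0.04/0.493 = 0.081.

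| p | 10-point gap, \|SMD\| (responds more / less) | 20-point gap, \|SMD\| (responds more / less) |
|---|---|---|
| 0.2 | 0.065 / 0.069 | 0.128 / 0.141 |
| 0.3 | 0.075 / 0.078 | 0.149 / 0.159 |
| 0.4 | 0.081 / 0.083 | 0.162 / 0.167 |
| 0.5 | 0.083 / 0.083 | 0.168 / 0.168 |

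All exceed the plan's own limit of 0.05. With g = 0, q = p and the expected SMD is 0. Expressed as response odds ratios at the same 60 % response and p = 0.2 to 0.5, an odds ratio of 1.5 gives 0.06 to 0.08 and an odds ratio of 2 gives 0.10 to 0.14.

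**3. Chance without differential response**

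The mailed pool copies the intervention group 10:1, so only the draw of 700 from 7,000 varies: SD of the SMD ≈ √[(1 − 0.1)/700] = √(0.9/700) = 0.036. Hence P(|SMD| > 0.05) = P(|Z| > 0.05/0.0359 = 1.39) ≈ 0.16 for one variable. If the six were independent and each a single number, P(at least one above 0.05) = 1 − (1 − 0.163)^6 ≈ 0.66. Correlation among them lowers this; several categories per variable raise it.

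**4. What this could do to the primary result**

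Bias in SD units ≈ SMD × the variable's residual standardised association with the outcome. Assuming an association of 0.1 to 0.2:
- SMD 0.08 gives 0.008 to 0.016, or 3 to 5 % of the planned effect of 0.3.
- SMD 0.17 gives 0.017 to 0.034, or 6 to 11 % of it.

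**The case against.** - **A defensible two-stage design.** Insurance variables shape the pool, and clinical prognostic variables then choose the twin. The score already holds baseline WOMAC, VR-6D, BMI, self-efficacy, activity, age, gender and morbidity. Age should capture much of pensioner status. This stands, and it limits the likely bias. It does not explain why a balance limit was written for costs and days but not for these six.
- **Further balance tables may sit in an analysis plan that is not shown.** That is fair for descriptive tables. But the recruitment section refers to the Statistics section for the detailed procedure, and that section gives an input list and a re-match trigger. The point concerns what those contain.
- **The size is assumed.** This stands. The protocol gives only an overall response rate from another study, and nothing on how response varies by education or employment.
- **Readings that go too far.** A reader might infer that costs and disability days can also drift apart. They cannot do so unchecked, because the 0.05 rule covers every such category. The economic evaluation also uses a double difference against two years before baseline, which removes stable level differences. A reader might also infer that the two sections define the twin in conflicting ways. They do not: the recruitment section speaks of a pool, never says that the twin must come from the participant's own ten, and defers to the Statistics section.

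**Conclusion.** The point holds for six variables: insurance type, complexity of work, level of education, highest attainment, contractual form and GP-centred care. Their exact balance is guaranteed only in the mailed pool. The stated propensity inputs, re-match rule and model covariate do not preserve or check it afterwards.

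A 10-point response gap would be enough to pass the plan's own limit (SMD about 0.07 to 0.08), and a 20-point gap would give about 0.13 to 0.17. These figures rest on assumed gaps and prevalences, 60 % response and no help from correlated score variables. The documents do not show that such gaps will occur, and the bias in the primary WOMAC comparison would probably be small. This is therefore a cheap improvement to a non-randomised comparison, not a flaw that overturns the design.

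Separately, the two statements on economic inputs need the same wording. One lists economic data as score inputs; the other admits costs and days only after a failed balance check. Conditional entry could be meant by both, so this is a matter of reconciliation.

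**What to change.** In the Statistics section on matching:

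1. Add the six variables to the inputs of the logistic regression for the propensity score. At the least, extend the SMD 0.05 check and the re-match rule to them, category by category. Adding them from the start is preferable, because the check alone would often be triggered by chance (about 0.16 per variable).
2. Complete this before any follow-up data are analysed, as the section already requires for the definition of twins.
3. State in both sections whether the cost and disability-day sums enter the score from the start or only when the SMD exceeds 0.05.

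The cost is wording and a somewhat larger propensity model. The insurer already extracts all six variables for step one, and the final matching already waits for the insurance data, so no new data collection is needed.

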
### Statistics

#### Sample size

Below are given details on the sample size estimation for primary clinical outcomes. However, aside from statistical power, a sufficiently large sample is necessary to obtain representative results for the general population and to allow sustainable statements on the effectiveness and efficiency of the intervention for secondary clinical as well as economic outcomes. We therefore plan to include all eligible patients willing to participate in the study and finally assume a number of n = 700 in each group. This number takes into consideration the degree of capacity utilization of hip and knee training courses as well as the number of subjects non eligible due to inclusion- and exclusion criteria as well as subjects refusing consent to participate in the study (Fig. 1).

The empirical basis of the sample size estimation for primary outcomes was retrieved from the paper by Krauss et al. [17]. In this randomized controlled trial (RCT), intra-individual differences of WOMAC subscale pain and WOMAC subscale physical function identically showed an effect size of about 0.5 between the intervention and the control group (pain, intervention: −8.5 ± 13.9, control: −1.3 ± 15.3, physical function, intervention: −8.4 ± 13.4, control: −2.1 ± 12.9).

Based on the previous results of the RCT and the so-called efficacy-effectiveness gap between RCTs and studies under real life conditions [32] we finally assume an effect size of ES = 0.3.

Due to the fact that we want to test the two endpoints (pain and physical function) simultaneously and without hierarchical order, we choose a level of significance of 0.025 (two-sided, Bonferroni correction) and a power of 0.90. This leads to a sample size of 278 subjects per group in the parallel group design without cluster effects (nquery release 7.0). The drop-out rate in the intervention group of the above mentioned RCT was 8 % [17]. As this value is quite low, we assume a somewhat higher number of non-finishers and estimate the rate to be 20 %. Thus 350 subjects should be allocated to each treatment arm.

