However, in our study, cluster effects may appear for subjects within identical training groups: We expect 700 included subjects participating in 170 different training courses. Thus four participants of each training group will averagely be subjects of the study (whereas the rest of the group participants are no study subjects). With a rather high intra class correlation of 0.33 we obtain a variance inflation factor of 2 for the intervention. Therefore, with 700 subjects per study arm the aimed power should be reached.

We refrain from analyzing our data using a matched-pair design as propensity score matching does not guarantee that individual pairs will be well-matched on the full set of covariates, only that groups of individuals with similar propensity scores will have similar covariate distributions [33]. Despite this fact, propensity score matching including among other variables baseline WOMAC scores as matching factors may reduce variance of outcome measures and therefore probably increase the power of the study further if the propensity score is included as covariate in the statistical evaluation model. However, it is difficult to quantify this effect and thus we conservatively calculated the sample size obtained for the parallel group design with cluster effect as described in the preceding paragraph.

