The finally defined controls and cases will be included into a linear model with the propensity score as covariate. Additionally, we will use models for longitudinal data using each measurement point (instead of only t0 and t3 for the primary analysis). The level of significance will be 0.025 for primary endpoints. Secondary endpoints will be analyzed analogously without claiming confirmatory interpretation of *p*-values.

Descriptive analysis will include absolute and percentage frequencies for categorical variables, means, medians, standard deviations, quartiles and ranges for quantitative variables and medians, quartiles and ranges for ordinal variables. For the main results, two-sided 95 % confidence limits will be given additionally to significance tests. For percentages exact confidence interval for proportions based on the binomial distribution will be given.

Exploratory, prognostic factors will be analyzed using multiple regression models (linear regression) to identify potential responders to the training.

Correlation analyses will use Pearson product moment correlation coefficient (normally distributed variables) and Spearman correlation (non-normally distributed variables).

The primary analysis will be done on the full set of patients recruited in consideration of the exclusion criteria “limited pain and impairment in physical function” (WOMAC Index subscales pain and physical function with values below 15) except for patients refusing consent during the study and obviously wrongly diagnosed patients. A secondary analysis will be done using the full set of eligible and included patients irrespective of their limitations in pain and physical function at baseline (t0). This secondary analysis will only claim confirmatory interpretation of p-values if the primary analysis is able to detect group differences in a statistical manner. Otherwise the secondary analysis will be done in an explorative manner.

Missing values will be imputed using multiple imputation approaches, complete case and last observation forward analysis will be performed as a sensitivity analysis. No interim analysis, except for administrative purposes will be performed. All statistical analysis will be done using the software SPSS and R in the newest release.

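### The stated primary model makes no allowance for training course, although the sample size check assumes clustering within courses, so run as written the 0.025 level is not held

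*Protocol article*

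**What the plan says.** The Sample size section sets the test: "we choose a level of significance of 0.025 (two-sided, Bonferroni correction) and a power of 0.90". For the effect, "we finally assume an effect size of ES = 0.3". This gives 278 per group without clustering. After an allowance of 20% for non-finishers, "Thus 350 subjects should be allocated to each treatment arm".

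The same section then raises dependence between patients: "However, in our study, cluster effects may appear for subjects within identical training groups". It expects 700 study patients in 170 courses, about four per course, and continues: "With a rather high intra class correlation of 0.33 we obtain a variance inflation factor of 2 for the intervention". It concludes that 700 per arm should reach the intended power.

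The section on matching procedures and statistical analysis of clinical endpoints states the primary model: "The finally defined controls and cases will be included into a linear model with the propensity score as covariate". The level is repeated there as 0.025. Longitudinal models are added and described by measurement point. Secondary endpoints are to be analysed in the same way. Neither these sentences nor any other section names a course effect or a standard error that allows for course.

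**The concern.** The two sections rest on different premises. The sample size check treats intervention patients in one course as correlated; the stated model, taken at its word, treats them as independent. Under the first premise the second gives a standard error that is too small. More patients do not cure this, because with about the same number per course the ratio of true to reported standard error is the same at any sample size.

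At stake are the p-values and confidence limits of both confirmatory endpoints. The secondary analysis, which ignores the baseline WOMAC limits, may claim confirmatory status if the primary analysis succeeds, so it would inherit the excess error. The longitudinal and secondary models share the omission.

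**Working it through.** **Inputs from the Sample size section.** Two-sided 0.025 per endpoint (critical value 2.2414), power 0.90, standardised effect 0.3, 20% loss, 700 patients in 170 courses (about 4 per course), ICC 0.33.

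**The plan's own figures.**
- Size per group without clustering: 276 by the normal approximation, 278 by the noncentral t. The stated 278 is reproduced.
- Loss: 278 / 0.80 = 347.5, so 348. The plan rounds to 350.
- Inflation factor: 1 + (4 − 1) × 0.33 = 1.99, or 2.03 with 700/170 = 4.12 per course. The stated 2 is reproduced, and 350 × 2 = 700.

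**Level of the model as written.** Courses exist only in the intervention arm, so inflation is VIF there and 1 among controls. With equal arms:
- true variance / model variance = (VIF + 1)/2 = (1.99 + 1)/2 = 1.495
- true SE / model SE = √1.495 = 1.223
- true two-sided level = 2 × [1 − Φ(2.2414 / 1.223)] = 0.067
- coverage of nominal 95% limits = 2 × Φ(1.96 / 1.223) − 1 = about 0.89
- Bonferroni bound over both endpoints = 2 × 0.067 = about 0.13 instead of 0.05

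**After 20% loss.** 560/170 = 3.29 per course; VIF = 1 + 2.29 × 0.33 = 1.76; SE ratio = √(2.76/2) = 1.174; level = 0.056.

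**Smaller ICCs.** These are assumed values, at 4 per course:

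| ICC | VIF | SE ratio | True level (nominal 0.025) |
|---|---|---|---|
| 0.01 | 1.03 | 1.007 | 0.026 |
| 0.05 | 1.15 | 1.037 | 0.031 |
| 0.10 | 1.30 | 1.072 | 0.037 |
| 0.20 | 1.60 | 1.140 | 0.049 |
| 0.33 | 1.99 | 1.223 | 0.067 |

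**Simulation.** With 170 courses of 4 against 680 independent controls, ICC 0.33 and 20,000 runs, the unadjusted test rejected in 0.068 of runs. A test using the variance between course means in the intervention arm rejected in 0.026.

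**Power once clustering is modelled.** With 560 completers per arm and VIF 1.99 in the intervention arm only, SE = √[(1.99 + 1)/560] = 0.0731, and power = Φ(0.3/0.0731 − 2.2414) = about 0.97. With VIF 2 in both arms it would be about 0.90.

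**The case against.** *The sentence is shorthand.* It names neither the group term nor the form of the outcome, a linear mixed model would fit its wording, and an analysis plan not at hand may add a course term. That is fair: the protocol is silent on clustering in the model and does not exclude it. But the model is stated, the propensity score is the one covariate named, and the Sample size section discusses the analysis model (rejecting a paired analysis, including the propensity score) directly after raising clustering, without bringing in the course. As stated, model and premise conflict.

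*The plan did not enlarge its sample for clustering.* A reader might infer that it doubled the sample for this reason. The documents do not support that. The 700 comes from course capacity, eligibility and consent, with economic and secondary outcomes as the reason for a large sample; the cluster calculation checks that 700 suffices. The check still needs an analysis that allows for clustering.

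*An ICC of 0.33 is a pessimistic value.* The protocol itself calls it high, says only that cluster effects may arise, and treats strong clustering as the unfavourable case in the Discussion. So 0.067 is the upper end and not a forecast. Excluding patients with low baseline WOMAC scores from the primary analysis would reduce the number per course further, although unequal course sizes work the other way.

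*The unpaired analysis may be conservative.* With residual within-pair correlation ρ, the variance ratio becomes (VIF + 1)/2 − ρ. Full offset needs ρ = 0.495 at ICC 0.33, 0.15 at 0.10 and 0.075 at 0.05. Part of the excess could vanish this way, but the documents give no value for ρ and say that individual pairs need not be well matched.

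**Conclusion.** The point holds for the model as written. The true level per endpoint is about 0.067 at the plan's own ICC and 4 patients per course, 0.056 at 3.3 per course, and 0.031 to 0.037 at assumed ICCs of 0.05 to 0.10. This assumes clustering in the intervention arm only, equal total variance in the two arms, equal course sizes and no within-pair correlation.

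Two stronger readings are not supported. A reader might infer that the error favours the exercise program. It does not: the estimate is not biased, and under the null hypothesis the excess rejections fall equally in both directions. What is overstated is significance and precision. A reader might also apply the factor of 2 to both arms, which would give a level of about 0.11, but controls attend no study course as part of the comparison and the protocol attaches the factor to the intervention.

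If the effect is as large as planned, the primary conclusion would seldom change, since power with clustering modelled is about 97%. The defect lies in the error rate and the confidence limits.

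**What to change.** In the section on statistical analysis of clinical endpoints, extend the primary model in one of two ways:
- a partially nested model, with a random intercept for training course in the intervention arm and each control as its own cluster; or
- the same linear model with robust standard errors clustered by course.

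Use the same choice in the longitudinal and secondary models.

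The statistical cost is somewhat wider intervals, which the planned size can absorb. There is also a practical cost. The Outcome measures section and its table list no course variable, and the data privacy section divides access between parties, so a pseudonymised course code must be passed to the analyst. The Blinding section keeps the statistician blind to group for the primary outcomes, and a code carried only by intervention patients would reveal it. Dummy cluster codes for controls, or applying the course code after the blinded steps, would keep that blinding as far as possible. The choice should be written down before the primary outcomes are analysed.
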